### Sample Size

Given the relative novelty of this application of olanzapine, no formal evaluation of the drug has yet been conducted on youth, making it difficult to accurately estimate sample size requirements. However, after consultation within our clinical team we believe that a decrease of 5 points on the EAT-26 scale would be clinically meaningful. The following assumptions were therefore used for sample size calculations: i) a minimal clinical important difference of 5 on the EAT-26 score; ii) an estimated standard deviation of 7.07; iii) two-sided test; iv) a power of 80% and a type I error of 5%; v) a provision for one interim analysis according to the O'Brien and Fleming criteria [35]. With these assumptions, the total sample size necessary is 64 participants. Anticipating a drop-out rate of at most 2.5%, the formula of Donner [36] may be used to adjust the sample size assuming an intention to treat analysis. The resulting total sample size is thus 67 participants (33 and 34 participants per treatment group). We anticipate that this study will take two years to complete enrollment.

### Statistical Analysis

Descriptive summaries of demographic and treatment balance will be generated with respect to all participant characteristics at baseline. Dichotomous variables will be summarized using percentages, normally distributed continuous variables will be summarized using means together with standard deviations, and continuous variables that are not normally distributed will be summarized using medians together with range.

Statistical analysis of the data will follow the intention-to-treat principle for the main analysis of treatment outcomes. For participants who develop clinical events that will lead to withdrawal from the study, or that are lost to follow-up prior to the 12-week primary endpoint, we will use the BMI plus last value captured for the EAT-26 test as a method of imputation of missing data.

A student's t-test (assuming a normal distribution of the measures; otherwise, Wilcoxon Mann-Whitney test will be used) will be used in order to compute the change between the EAT-26 and the difference in BMI from baseline to week 12. If necessary, a linear regression model will be fit to assess treatment effect adjusting for variables thought to influence outcome that could result in imbalance between treatment groups at baseline. Treatment effect and its 95% confidence interval will be generated for each primary outcome.

To examine secondary outcomes, the differences between study groups will be assessed using Student's t-tests (as described above for primary outcome). In order to avoid multiple testing issues, results will be compared with an alpha value adjusted for the number of tests performed using the Bonferonni criterion.

Although the study is not powered to detect differences in safety, we will nevertheless compare the frequency of adverse events between the two study groups using chi-square or Fisher's exact test.

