It is hypothesized that adolescents who are diagnosed with a severe eating disorder and are treated with olanzapine will demonstrate reduced disordered eating attitudes and behaviours as well as an increased rate of weight gain, as compared to a control group treated with placebo. It is also hypothesized that patients treated with olanzapine will demonstrate better long-term clinical outcomes in comparison to patients treated with placebo. It is also predicted that the adverse effects of olanzapine will be minor given the relatively low dose (as compared to treatment for patients with schizophrenia), slow titration, and short-term use of olanzapine.

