#### Secondary Outcome Measures

Change from baseline in the EAT-26 score measured at week 6, 15 (i.e. off medication) and at the end of the maintenance period (week 40), as well as BMI change measured at the same time points will be analyzed as for the primary outcomes. Change from baseline in the CAPI, the CDI, the MASC, the EDS3 and the CBCLwill be calculated for weeks 6, 12, 15 and 40.

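### The week-40 comparison, the test of the long-term hypothesis, has no clear missing-data rule: it may use returners only or values carried forward 25 weeks or more, and one repeated-measures model would avoid both

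*Protocol article*

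**What the plan says.** All references are to the protocol article.

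- **Background** predicts that "patients treated with olanzapine will demonstrate better long-term clinical outcomes in comparison to patients treated with placebo".
- **Secondary Outcome Measures** lists change in EAT-26 and BMI at weeks 6, 15 and 40, to be handled in the same way as the primary outcomes. It also lists change in CAPI, CDI, MASC, EDS3 and CBCL at weeks 6, 12, 15 and 40.
- **Statistical Analysis** gives one missing-data rule. For participants withdrawn after clinical events "or that are lost to follow-up prior to the 12-week primary endpoint", it says "we will use the BMI plus last value captured for the EAT-26 test as a method of imputation of missing data". No other scale is named.
- The same section continues: "To examine secondary outcomes, the differences between study groups will be assessed using" Student's t-tests, with a reference back to the primary analysis and a Bonferroni adjustment. No model joining the visits is mentioned.
- The same section says that the analysis "will follow the intention-to-treat principle for the main analysis of treatment outcomes".
- **Table 1** has weekly visits up to Day 105 (week 15) and then one visit at Day 280 (week 40).
- **Sample Size** gives the only drop-out figure, at most 2.5%.

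**The concern.** The long-term hypothesis depends on the visit that is most exposed to loss, and the written rule for loss to follow-up ends at week 12. A participant seen up to week 15 but not at week 40 has no clearly stated place in the week-40 test.

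For the five scales other than EAT-26, a t-test on week-40 change can use only those who come back. For EAT-26 and BMI there are two candidate analyses:

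- **Returners only.** If participants who were doing badly at week 15 return less often, and the arms differ at week 15, loss differs by arm and the week-40 difference is distorted.
- **Carry-forward.** The carried value dates from week 15 or earlier, so an effect seen at or shortly after treatment is reported as a week-40 effect.

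Because the text supports both readings, the choice could be made after the data are seen, and it would move the long-term estimate.

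**Working it through.** **1. The plan's own figures.** With a difference of 5, SD 7.07, two-sided 5% and 80% power, n per arm = 2 × [7.07 × (1.960 + 0.842) / 5]² = 31.4. This rounds up to 32, or 64 in total, as stated. Then 64 / 0.975² = 67.3, which matches the stated 67. The SD and difference are therefore usable as inputs.

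**2. The gap.** (280 − 105) / 7 = 25 weeks from week 15 to week 40. From week 12 (Day 84) it is (280 − 84) / 7 = 28 weeks. A value carried forward to week 40 would be at least 25 weeks old.

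**3. What the rules cover at week 40.**

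| Outcome | Rule for a missing week-40 value | Natural result |
|---|---|---|
| CAPI, CDI, MASC, EDS3, CBCL | none named | returners only |
| EAT-26, BMI | loss rule ends at week 12, but later visits are to be analysed like the primary outcomes | returners only, or carry-forward |

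**4. Size on the EAT-26 scale.**

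- From the plan: SD 7.07, a 5-point difference (placed here at week 15), arms of 34 and 33.
- Assumed, because the document gives no figure: true week-40 difference 2.5, correlation 0.6 between week-15 and week-40 change, and loss at week 40 rising with a worse week-15 change (logistic, slope 0.14 per point, intercept set to the overall loss).
- Estimators: returners-only difference in means; difference in means with week 15 carried forward; likelihood estimate, which regresses week 40 on arm and week 15 in returners and evaluates it at the week-15 means of all participants.

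Estimated week-40 difference in favour of olanzapine (truth 2.5):

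| Overall loss (olanzapine / placebo) | Returners only | Carry-forward | Likelihood |
|---|---|---|---|
| 35% (28% / 42%) | 2.1 | 3.3 | 2.5 |
| 20% (15% / 25%) | 2.2 | 3.0 | 2.5 |
| 10% (7% / 13%) | 2.3 | 2.8 | 2.5 |
| 2.5% (1.7% / 3.3%) | 2.4 | 2.6 | 2.5 |

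Over 3,000 simulated trials at 35% loss, the standard deviation of the estimate was about 2.1 for returners only and 2.0 for the likelihood model.

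**5. Carry-forward when loss is unrelated to outcome.** The expected estimate is 0.65 × 2.5 + 0.35 × 5 = 1.625 + 1.75 = 3.4, about a third above the truth. Returners-only is unbiased in that case.

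**6. The direction for returners-only is not fixed.** Suppose there is no true effect, half of each arm is 10 points worse, and 90% of these return in one arm but 50% in the other. Returner means are 10 × 0.45 / 0.95 = 4.7 and 10 × 0.25 / 0.75 = 3.3, a spurious difference of 1.4 points. With equal return in both arms the difference is zero.

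**The case against.** **The text does not state a returners-only analysis.** A reader might infer that every participant missing at week 40 is dropped. For EAT-26 and BMI this does not follow, because both Secondary Outcome Measures and Statistical Analysis refer back to the primary analysis, which can include its imputation. The time limit attaches to loss to follow-up, so withdrawal for clinical events may be covered at any time. This stands, and it is why the point is put as two readings. It does not help the five other scales, for which no imputation is named.

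**Three further inferences are tempting but unsupported.**

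- Intention-to-treat is not contradicted: it is promised for the main analysis, and week 40 is secondary.
- Earlier assessments are not discarded altogether. Baseline enters every change score and weeks 6, 12 and 15 have their own comparisons. They go unused only in the week-40 contrast.
- Week 15 does not share the 25-week gap. It follows weekly visits, and Table 1 uses the same visit for early termination.

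**The size rests on chosen inputs.** This stands. In the assumed setting loss depends only on the observed week-15 value, which is exactly what the likelihood model requires, so its lack of bias is built in. The returners-only bias of about 0.4 points at 35% loss is small beside a standard deviation of about 2.1, and interval coverage in that setting was still 94%.

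**Missing-data detail for secondary visits commonly belongs in the analysis plan.** This stands for mere omission. Here, however, the article fixes separate t-tests and a rule with a week-12 boundary. An analysis plan that follows it inherits the ambiguity, and one that uses a joint model departs from it.

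**Conclusion.** The concern holds in limited form. At week 40 the plan most naturally compares returners only for CAPI, CDI, MASC, EDS3 and CBCL. For EAT-26 and BMI it leaves open whether returners or carried-forward values are compared. Under the assumed inputs the two readings fall on opposite sides of the truth: about 2.1 and 3.3 against 2.5 at 35% loss, and about 2.3 and 2.8 at 10%. If loss at week 40 stays near the 2.5% used for sample size, the choice hardly matters. However, the article does not say that this figure was meant to cover the 25-week interval.

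The primary week-12 analysis is not touched by this point. The case for change is that week 40 is the furthest test of a stated hypothesis and that the data needed for a better analysis are already collected.

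**What to change.** For EAT-26, BMI and each of the five other scales, replace the separate week-40 t-test, and any carry-forward to week 40, by one likelihood-based repeated-measures model. Use change at weeks 6, 12, 15 and 40 as the response, with arm, visit, arm-by-visit and the baseline value as terms and an unstructured covariance. Include everyone with at least one post-baseline value, and read the week-40 contrast and its confidence interval from the model. State explicitly that the week-12 imputation rule does not extend to week 40.

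Report the number and share missing at week 40 by arm, and show the returners-only result as a sensitivity analysis.

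**Cost:** wording only, with no new visits, measures or participants. The small downside is that the model assumes loss is explained by the values already observed. If return depends on the unseen week-40 state, as in the two-class example in the working, bias can remain, so the sensitivity result and the loss by arm need to be shown beside it.

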Clinicians will be asked to complete the **Eating Disorder Symptom Severity Scale **(EDS3) [33] which will examine their observations of the youth's eating disorder symptoms such as: dieting behaviours, body image preoccupations, agitation related to eating/body image, fear of fat, food anxiety, as well as overall motivation for treatment. Clinicians involved in the study have attended a workshop meant to improve inter-rater reliability for this scale (r = .75 to r = .80 was deemed acceptable)

Parents will be asked to complete the **Child Behavior Checklist **[34] in order to evaluate their perceptions of their child's mood and anxiety. The Child Behaviour Checklist (CBCL) has been demonstrated to be a reliable measure when completed by parents, with a mean alpha 0.80 being reported [34]. The CBCL is a widely used, well-validated instrument in pediatric populations.

The psychological measures will be completed at baseline, weeks 6, 12, 15 and 40 (see Table 1). The patient will complete the EAT, CDI and the MASC; the parent will complete the CBCL; and the treating physician and therapist will complete the CAPI and EDS3.

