### Medical Monitoring (see Table 1 for Schedule of Events)

The baseline medical assessment will include a physical examination, monitoring of side effects/symptoms (utilizing the side-effect checklist), completion of the Acquired Involuntary Movement Scale (AIMS) to monitor extrapyramidal symptoms, taking of vital signs (temperature plus lying and standing heart rate and blood pressure), an EKG, bone mineral density, and comprehensive lab work (see Table 1). An EKG will be repeated at Weeks 2, 4, and 15. At each clinic visit, a urine sample (urinalysis and pregnancy test) will be taken, vital signs completed, and weight recorded.

The AIMS and an adverse event checklist are also completed at each clinic visit.

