#### Primary Outcome Measures

The primary outcome measure will be the change from baseline on the total score of the EAT-26 score measured at week 12 prior to topping off the medication, and BMI change over the first 12 weeks of treatment.

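### Last-value imputation of missing week-12 EAT-26 scores in the main analysis shrinks or distorts the treatment effect once drop-out passes the very low planned rate, and the BMI rule in the same sentence is unclear

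*Protocol article*

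**What the plan says.** The Primary Outcome Measures section sets two outcomes. The first is EAT-26: "The primary outcome measure will be the change from baseline on the total score of the EAT-26 score measured at week 12". The second is BMI change over the same 12 weeks.

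The Statistical Analysis section declares the framework: "Statistical analysis of the data will follow the intention-to-treat principle for the main analysis of treatment outcomes". It then names two groups whose missing values are imputed. One is defined by clinical events: "For participants who develop clinical events that will lead to withdrawal from the study". The other is everyone whose follow-up ends early, before the week-12 assessment. The method for both is: "we will use the BMI plus last value captured for the EAT-26 test as a method of imputation of missing data". The completed data go into a t-test, or a Wilcoxon Mann-Whitney test if normality fails. The article names no other method for missing data.

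On timing, the Psychological Measures section states: "The psychological measures will be completed at baseline, weeks 6, 12, 15 and 40". Table 1 agrees, and also marks EAT-26 in the column shared by week 15 and termination. Weight is different: at each clinic visit the Medical Monitoring section has "vital signs completed, and weight recorded", and Table 1 shows weight and BMI weekly to week 15.

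**The concern.** The imputation rule is stated, not left open, and it governs the main analysis of a primary outcome. It assumes that a participant's EAT-26 score stays where it was when last measured. The design makes that doubtful. Both arms receive psychological, nutritional and medical care throughout, so scores are expected to move, and only one scheduled EAT-26 value lies between baseline and the endpoint.

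Two consequences follow. Every drop-out is credited with only part of the change, so a real difference shrinks even when drop-out is equal. When drop-out is unequal, the arm losing more participants is credited with less improvement, which can create or hide a difference. The article gives reasons for imbalance in either direction: it names sedation and allows for intolerable side effects, but it also cites better compliance on olanzapine. The t-test then treats the filled-in values as if they had been observed.

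**Working it through.** **Inputs from the protocol article.** Target difference 5 points, SD 7.07, two-sided 5%, power 80%, drop-out at most 2.5%, total 67 (Sample Size); final alpha 0.048 (Interim analysis); EAT-26 at weeks 0, 6 and 12 (Table 1).

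**Assumptions, because the article gives no figure.** Mean improvement on placebo of 5 or 10 points, drop-out by arm, and the share *c* of the full change credited to a drop-out: *c* = 0 if baseline is carried; *c* = 0.5 if the week-6 value is carried and half the change has occurred by then; *c* = 0.25 for an even mix.

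**Step 1: the plan's own figures.** n per arm = 2 × (1.960 + 0.842)² × 7.07² / 5² = 31.4, so 32 per arm and 64 in total. Inflated for drop-out, 64 / (1 − 0.025)² = 67.3, which matches 67. The sample size is reproduced and is not at issue.

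**Step 2: formula.** With true mean improvement *m* and drop-out *d*, carry-forward credits an arm with *m* × (1 − *d* + *d* × *c*). The expected estimate is the difference between arms.

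**Step 3: planned drop-out, 2.5% in each arm** (67 × 0.025 = 1.7 participants). A true 5 becomes 5 × 0.975 = 4.88 (*c* = 0) or 5 × 0.98125 = 4.91 (*c* = 0.25). This is negligible.

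**Step 4: equal drop-out, true difference 5.**
- 10% in each arm: 5 × 0.90 = 4.5, or 5 × 0.925 = 4.63.
- 20% in each arm: 5 × 0.80 = 4.0, or 5 × 0.85 = 4.25.

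**Step 5: unequal drop-out, no drug effect, both arms improving 10 points.**
- 5% against 20%: baseline carried, 9.5 − 8.0 = 1.5; week 6 carried, 9.75 − 9.0 = 0.75.
- 10% against 30%: baseline carried, 9.0 − 7.0 = 2.0; week 6 carried, 9.5 − 8.5 = 1.0.

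Against the 5-point target these are 15% to 30% and 20% to 40%. In a simulation of 10% against 30% (33 per arm, 8,000 runs, drop-out at random, *c* = 0.25) the false difference was about 1.5 points. The test at 0.048 rejected in 13% to 14% of runs, and the 95% interval covered the truth in about 86%.

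**Step 6: unequal drop-out, true difference 5, placebo improvement 5** (so olanzapine 10).
- 30% olanzapine, 10% placebo: 7.0 − 4.5 = 2.5 (*c* = 0) or 7.75 − 4.625 = 3.1 (*c* = 0.25). Simulated power with *c* = 0.25 was 41%, against 70% using observed week-12 values only.
- 10% olanzapine, 30% placebo: 9.0 − 3.5 = 5.5, or 9.25 − 3.875 = 5.4.

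**Step 7: standard error, Step 5 scenarios with baseline carried, 33 per arm.** The imputed variance in an arm is (1 − *d*) × 50 + *d*(1 − *d*) × 10², using 7.07² ≈ 50.
- 5% against 20%: √[(52.25 + 56) / 33] = 1.81, against √[50/(33 × 0.95) + 50/(33 × 0.80)] = 1.87 from observed values; about 3% smaller.
- 10% against 30%: √[(54 + 56) / 33] = 1.83, against 1.96; about 7% smaller.

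With a smaller mean change the gap widens. In the simulations with placebo improvement 5 and true difference 5, the values were 1.72 against 1.95 at 20% in each arm (12% smaller) and 1.69 against 2.08 at 30% (19% smaller). With placebo improvement 10 the gap was 3% at 20% in each arm and nil at 10%.

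**The case against.** The strongest reply is that the only drop-out figure in the article is at most 2.5%, about two participants, and at that rate the rule is harmless. That stands. Every material figure above rests on drop-out and improvement rates that the article does not give. Still, an imputation rule matters only when drop-out exceeds expectation, and a 2.5% allowance leaves little margin.

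Second, Table 1 provides an EAT-26 at termination. A participant who leaves early but attends that visit carries an exit value, not baseline. This also stands: the baseline-carried figures are upper bounds. An exit value can still differ from the week-12 value, so the bias shrinks without vanishing.

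Three stronger readings are tempting but unsupported:
- A reader might infer that drop-outs are frozen near baseline on both primary outcomes. That fits EAT-26 only. Weight is recorded weekly, so a carried BMI could be recent, and the sentence does not say which BMI value is used.
- A reader might infer that stopping study drug ends assessment and so creates the missing data. The rule covers participants withdrawn from the study or lost; the article does not say that stopping drug ends follow-up.
- A reader might infer that the standard error is always badly understated. The size depends on the mean change, because zeros added to a large mean change widen the spread. In the simulations the carry-forward standard error also agreed with the estimator's own sampling variation; it is too small relative to the information in the observed week-12 data. The poor interval coverage comes mainly from bias.

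**Conclusion.** The point holds in limited form. Carrying the last EAT-26 value to week 12 in the main analysis is a weak rule given a single scheduled interim measurement and ongoing care in both arms. It shrinks a real effect under equal drop-out (5 to about 4.0 to 4.25 points at an assumed 20%). Under unequal drop-out it biases the comparison in either direction: up to 0.75 to 1.5 points at 5% against 20%, and 1 to 2 points at 10% against 30%, assuming no drug effect and a 10-point improvement in both arms. The apparent gain in precision is about 3% to 7% in those baseline-carried scenarios and larger when mean change is smaller.

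The effect is negligible at the planned 2.5% and starts to matter at about 10% drop-out or with clear imbalance. The rule should be changed, but it does not invalidate the trial as planned. The unclear BMI wording needs correction whatever the drop-out.

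**What to change.** 1. Make the primary analysis a likelihood-based repeated-measures model with the treatment contrast at week 12. For EAT-26 use baseline, week 6 and week 12, with baseline in the outcome vector so that participants with only a baseline value are retained. For BMI use baseline and the weekly visits.
2. State that this model assumes data are missing at random, and that participants with no post-baseline EAT-26 add little information to the week-12 contrast.
3. Keep last observation carried forward as a sensitivity analysis, beside a delta-adjusted multiple imputation that departs from missing at random.
4. Rewrite the imputation sentence so that the rule for BMI is explicit.
5. State that EAT-26 and BMI are collected to week 12 in participants who stop study drug but remain in the clinic's care. If the full protocol already provides this, say so.

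The cost is revised wording, slightly more programming and a few off-drug assessments. The sample size does not change.

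### The primary analysis is an unadjusted test of change with regression only as an undefined option; one prespecified baseline-adjusted model per outcome would be generally more precise and would settle which result counts

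*Protocol article*

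**What the plan says.** Under Primary Outcome Measures, the article states: "The primary outcome measure will be the change from baseline on the total score of the EAT-26 score measured at week 12". BMI change over the first 12 weeks is named alongside it.

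The Statistical Analysis section tests these changes with a Student's t-test, under this condition: "assuming a normal distribution of the measures; otherwise, Wilcoxon Mann-Whitney test will be used". The test "will be used in order to compute the change between the EAT-26 and the difference in BMI from baseline to week 12". A regression may follow: "If necessary, a linear regression model will be fit to assess treatment effect adjusting for variables thought to influence outcome". The variables it would adjust for are those "that could result in imbalance between treatment groups at baseline". The section then promises a treatment effect with a 95% confidence interval for each primary outcome, without saying which of these analyses supplies it.

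The baseline values needed for adjustment are already collected. For EAT-26: "The psychological measures will be completed at baseline, weeks 6, 12, 15 and 40". Table 1 schedules weight and BMI at week 0 and week 12.

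**The concern.** Two things follow from this text.

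**Precision and conditional bias.** A t-test of change subtracts the whole baseline value, which amounts to assuming a baseline slope of exactly 1. ANCOVA estimates that slope. Where the true slope is below 1, the change score carries avoidable noise. If chance then leaves one arm with a higher baseline, that arm is expected to fall further through regression to the mean, and the change score counts this as treatment effect.

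**An open choice in the confirmatory test.** The article gives the regression a condition but no criterion, and it does not rank the regression against the t-test. If the two fall on opposite sides of the significance level, the text does not say what the trial concludes. The same question arises at the interim analysis, which also covers the primary outcome.

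**Working it through.** **Inputs from the article.** Sample Size: "a minimal clinical important difference of 5 on the EAT-26 score"; SD 7.07; two-sided test; 80% power; 5% type I error; 64 patients, raised to 67 (33 and 34 per arm). Interim analysis: final alpha 0.048.

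**Assumptions not in the article.** The correlation rho between baseline and week 12; the ratio k of the week-12 SD to the baseline SD; and that 7.07 is the SD of change (the article does not say what it is the SD of).

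**1. The plan's own figure.** n per arm = 2 × (7.07 × (1.960 + 0.842) / 5)² = 31.4, rounded up to 32, so 64 in total. The stated number reproduces, and it belongs to an unadjusted comparison. Dropout: 64 / (1 − 0.025)² = 67.3, consistent with 67.

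**2. Variance ratio.** In units of the baseline variance:
- change score: 1 + k² − 2·rho·k
- ANCOVA residual: k²(1 − rho²)

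With k = 1 the ratio of ANCOVA to change is (1 − rho²) / (2(1 − rho)) = (1 + rho)/2. In general the gain vanishes when the slope, rho × k, equals 1.

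**3. Power.** Non-central t, 33 and 34 patients, alpha 0.048, difference 5, SD = 7.07 × √ratio. The unadjusted test has 80.9%.

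| rho | ratio, k = 1 | power | ratio, k = 1.25 | power |
|---|---|---|---|---|
| 0.3 | 0.65 | 94.0% | 0.78 | 89% |
| 0.5 | 0.75 | 90.5% | 0.89 | 85% |
| 0.7 | 0.85 | 86.7% | 0.98 | 82% |
| 0.8 | 0.90 | 84.8% | 1.00 | 81% (no gain) |

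At rho 0.8 and k = 1.25 the slope is 0.8 × 1.25 = 1, which is why nothing is gained. The degree of freedom lost to the covariate changes these figures by less than 0.1 point.

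**4. If 7.07 is the SD of the raw score (k = 1, alpha 0.05, 80% power).** The change-score test needs 88, 64 and 38 patients in total at rho 0.3, 0.5 and 0.7; ANCOVA needs 58, 48 and 34. The direction is the same.

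**5. Size of the conditional bias.** Given a baseline gap D between arms, the change score is off by (1 − slope) × D. The standard error of D is √(1/33 + 1/34) = 0.244 baseline SDs, so a gap above 0.25 SD in either direction has probability of about 31%, and above 0.5 SD about 4%. At rho 0.5 and k = 1 the baseline SD implied by 7.07 is 7.07 / √(2 × 0.5) = 7.07. A 0.25 SD gap is then 1.77 points and the bias 0.5 × 1.77 = 0.88 points, against a target of 5.

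**6. Type I error.** Simulated under the null: 32 per arm, normal data, 10,000 runs for each of rho 0.3, 0.5 and 0.7, nominal 0.05.
- t-test or Wilcoxon chosen by a Shapiro-Wilk pretest: 0.051 to 0.054.
- ANCOVA substituted only when baseline differs at p < 0.10: 0.040 to 0.047.
- More favourable of the planned test and ANCOVA reported: 0.082, 0.074 and 0.070.
- ANCOVA fixed in advance: 0.050.

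**The case against.** The planned test is valid over randomisation, matches the stated outcome and reaches its planned power without adjustment. That stands: this point concerns efficiency and clarity, not a broken test.

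The size of the gain is uncertain. The (1 + rho)/2 formula needs equal SDs at both times, and the condition for no gain is a slope of 1, not a correlation of 1. Unequal SDs are plausible for BMI, because an entry limit of 17.5 truncates its baseline distribution, and the article gives no SD for BMI at all. This also stands, and the gain is therefore shown as a range for EAT-26 only.

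An unseen analysis plan could supply the normality criterion, the covariates and the trigger. That is fair for such details. But the article itself fixes an unadjusted test as primary and makes adjustment conditional, so that choice is open to comment.

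A reader might infer more than the text supports:
- *That the baseline is wasted.* It is not: a change score uses it, with a fixed slope.
- *That type I error is inflated.* The normality switch and an imbalance-triggered adjustment stay near or below nominal. Inflation to about 0.07 to 0.08 needs the better of two results to be picked, which the article does not provide for.
- *That Wilcoxon breaks a promise of a mean difference.* The article promises a treatment effect with an interval, and a Hodges-Lehmann shift with its interval could accompany Wilcoxon.
- *That adjustment definitely waits for observed imbalance.* The wording could also describe prognostic variables chosen on prior grounds.

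**Conclusion.** The point holds as an improvement that should be made. The article fixes an unadjusted change-score test, leaves regression to an undefined condition and does not say which result prevails. Prespecified baseline adjustment would raise power from 81% to between 85% and 94% for rho from 0.8 down to 0.3, if 7.07 is the SD of change and the SDs at the two times are equal. With a week-12 SD 1.25 times the baseline SD, the corresponding range is from no gain (81%) to 89%. Rho and the SD ratio are assumptions; the article supplies neither. In samples of this size adjustment costs almost nothing when it does not help, and it removes the conditional bias from chance baseline differences. The documents do not show that the planned test is invalid, underpowered on its own assumptions, or inflated in type I error when followed as written.

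**What to change.** Name one primary model for each primary outcome: the week-12 value (EAT-26; BMI) regressed on treatment and its own baseline value. Fit it whatever baseline imbalance or distribution is observed, and take the treatment effect, 95% confidence interval and test from it at both the interim and the final analysis. Using change as the response in the same model gives the identical treatment estimate, so the outcome definition need not be altered. Any further covariates should be named in advance. Remove the conditional adjustment, and keep the t-test of change and Wilcoxon as sensitivity analyses.

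The cost is wording only: no new data and no new visits. The sample size of 67 can stand.

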### Interim analysis

One interim analysis will be run after the enrolment of the 33^rd ^patient, which will be representative of half of the sample. This analysis will focus on the primary outcome and safety issues. Using the O'Brien-Fleming criteria for two-sided test, the alpha-level of this interim analysis will be 0.005. The final analysis will be conducted using an alpha-level of 0.048.

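### The promised 95% confidence interval matches neither the 0.005 interim test nor the 0.048 final test: a minor mismatch at the final analysis, and an overstatement of precision if the trial stops early

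*Protocol article*

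**What the plan says.** Three sections of the protocol article bear on this.

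- **Statistical Analysis**, on the two primary outcomes (EAT-26 change and BMI change to week 12): "Treatment effect and its 95% confidence interval will be generated for each primary outcome". The sentence does not say how the interval is built, does not mention the interim analysis and does not make the interval a decision rule.
- **Interim analysis**: one look after the 33rd patient, "which will be representative of half of the sample". On its content: "This analysis will focus on the primary outcome and safety issues". On the thresholds: "Using the O'Brien-Fleming criteria for two-sided test, the alpha-level of this interim analysis will be 0.005", and then "The final analysis will be conducted using an alpha-level of 0.048".
- **Sample Size**: an overall two-sided type I error of 5%, with one interim analysis by the O'Brien-Fleming criteria already allowed for.

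**The concern.** A two-sided 95% interval excludes zero exactly when the corresponding test has p below 0.05. This trial tests at 0.005 and then at 0.048, so an ordinary 95% interval belongs to a decision rule that the trial does not use.

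Two consequences follow. At the final analysis, a p-value between 0.048 and 0.05 would be declared non-significant beside an interval that excludes zero. If the trial stops at the interim, the published interval would take no account of the selection that caused the stop, and its stated 95% would not be its actual coverage. What is at stake is the honesty of the reported precision, not the error control of the test.

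**Working it through.** **Inputs.** From the article: alphas 0.005 and 0.048; interim at half the sample; planning SD 7.07; target difference 5 points; arms of 33 and 34. Assumptions made here: the SD applies to the EAT-26 change, the 33 interim patients split 16/17, and crossing 0.005 stops the trial for efficacy. The article gives no SD for BMI, so results in points concern EAT-26 only. Results in p-values concern both outcomes.

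**1. The plan's own thresholds reproduce.** For two equally spaced looks and overall two-sided 0.05, the O'Brien-Fleming boundaries are 1.977 × √2 = 2.797 and 1.977. The nominal alphas are 2(1 − Φ(2.797)) = 0.0052 and 2(1 − Φ(1.977)) = 0.0480, which round to the stated values. Testing at 0.005 and then 0.048 gives an overall error of 0.0499. The test procedure is sound.

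**2. Final analysis.** SE = 7.07 × √(1/33 + 1/34) = 1.728.

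- 95%: critical t on 65 df = 1.997, half-width 1.997 × 1.728 = 3.45 points.
- 95.2% (matches 0.048): critical t = 2.015, half-width 2.015 × 1.728 = 3.48 points.
- Ratio 2.015/1.997 ≈ 1.009, so the 95% interval is about 0.9% too narrow.

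Test and interval disagree only for 0.048 ≤ p < 0.05, that is, for an observed difference between 3.45 and 3.48 points. Ignoring the interim look, the probability that |Z| falls between 1.960 and 1.977 is 0.2% with no effect, 0.45% at a true 5 points and at most 0.7% for any effect. The disagreement goes one way: the interval can exclude zero while the test fails, never the reverse.

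**3. Width at the interim.** Critical t on 31 df is 3.022 at 99.5% and 2.040 at 95%, a ratio of 1.48. With SE = 7.07 × √(1/16 + 1/17) = 2.463, the half-widths are 7.44 and 5.02 points.

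**4. Coverage after an early stop** (normal approximation, half information, interim SE = 1.728 × √2 = 2.443).

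At a true effect of 5 points the interim Z has mean 5/2.443 = 2.046.

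- Stop: P(Z > 2.807) = 1 − Φ(0.761) = 0.223.
- Stop and 95% interval covers 5: Φ(1.960) − Φ(0.761) = 0.975 − 0.777 = 0.198.
- Coverage among stopped trials: 0.198/0.223 ≈ 0.89.
- Same for a 99.5% interval: (0.9975 − 0.777)/0.223 ≈ 0.99.

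At a true effect of 2.5 points the mean is 1.023. Stopping is rare (3.7%), and coverage among stopped trials is (Φ(1.960) − Φ(1.784))/0.037 ≈ 0.33 for the 95% interval, against 0.93 for the 99.5% interval.

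**5. Coverage over all trials.** Add the probability of stopping with a covering interval to the probability of continuing with a final interval that covers. The two Z statistics have correlation √0.5.

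| True effect (points) | Ordinary 95% at the look reported | Matched 99.5% / 95.2% |
|---|---|---|
| 0 | 94.8% | 95.0% |
| 2.5 | 93.6% | 96.0% |
| 5 | 94.7% | 97.1% |

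**The case against.** The strongest reply is that nothing is contradictory. The Interim analysis section fixes the decision rule clearly, the Statistical Analysis section only promises an estimate with an interval, and a conventional 95% interval beside a sequentially adjusted test level is common reporting. That stands: this is not an error in the design.

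The article also does not say that the interval is unadjusted. A sequentially adjusted interval can itself be a 95% interval, and a fuller protocol or analysis plan may define one. That is fair, and in that case the sentence only needs to say so. Read as written, however, the ordinary interval is the natural meaning.

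Two stronger readings are tempting, and the article does not support them.

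- A reader might infer that test and interval can give opposite verdicts at an interim stop. They cannot: a trial that stops at p < 0.005 always has a 95% interval excluding zero, and a trial that continues is judged at the final analysis.
- A reader might infer that success could be declared from a 95% interval at both looks, inflating the type I error. The article plans no such rule.

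Conditional coverage also needs care. When the true effect is zero, every trial that crosses the boundary has an interval excluding zero, at 95% or at 99.5%. The matched interval repairs coverage over all trials and most of the loss at real effects, but not every conditional case. It is also conservative, covering 97.1% overall at 5 points.

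**Conclusion.** The mismatch is real and small. At the final analysis it amounts to a 0.9% difference in width and a one-directional disagreement in at most about 0.7% of trials, which alone would hardly matter. After an early stop for efficacy it is more than cosmetic: the ordinary interval's coverage is about 89% among stopped trials at the planned 5-point effect, and its coverage over all trials falls to about 93.6% at 2.5 points.

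The early-stop result rests on the 0.005 boundary being used to stop for efficacy, which the article implies but does not state outright, and on the planning SD and a normal approximation. Sample size, power and the planned 5% type I error are unchanged. This is a reporting correction worth making, not a flaw in the design.

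**What to change.** In the Statistical Analysis section, replace the sentence on the interval with one that does three things:

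- reports the final primary treatment effects with a 95.2% interval, matching the 0.048 test;
- says that if the trial stops at the interim, a sequentially adjusted interval will be reported, for example the 99.5% repeated confidence interval matching the 0.005 test;
- states that significance is judged by the thresholds in the Interim analysis section.

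The cost is one sentence, a final interval about 1% wider and a conservative interval after an early stop. Fixing it before any unblinded result is seen also removes a later choice between intervals in a borderline or early-stopped trial.
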